### Screening measures

A two-stage screening is set up to ascertain whether or not participants fulfill the eligibility criteria. Stage 1 is an online rapid screening and is conducted in the Chinese language. Participants are screened for the aforementioned inclusion criteria 1 to 9, as well as for the aforementioned exclusion criteria 1 to 6. Demographic information is collected, including Hong Kong residency, age, predominant sleep complaints, and the extent of the resulting distress or impairment in social, occupational, and other important areas of functioning. Participants are asked if they are able to read Chinese and type Chinese or English, have a smartphone device (iOS or Android operating system) with Internet access, and have a regular email address. Participants’ severity of insomnia symptoms is measured by the Insomnia Severity Index [29], and each item is rated on a 4-point Likert scale, ranging from “not at all” to “extremely.” It has been validated in Hong Kong samples [30, 31] and has high internal consistency (Cronbach’s alpha = .81 [31]). Participants’ severity of depressive symptoms is measured by the PHQ-9, and each item is rated on a 4-point Likert scale, ranging from “not at all” to “nearly every day.” It has been validated in Hong Kong samples [32] and has high internal consistency (Cronbach’s alpha = .82 [32]). Participants’ suicidal ideation is assessed by BDI-II item 9. Participants are asked to indicate whether they are receiving any concurrent psychological treatment at least once per month, whether they had participated in the proACT-S pilot clinical trial, whether they are currently taking prescribed psychiatric medication regularly, whether they are diagnosed with psychosis or schizophrenia, and whether they are participating in any other academic studies or clinical trials related to insomnia and/or depression.

Stage 2 is a telephone diagnostic interview screening and is conducted in Cantonese. It is used to assess clinical depression and insomnia, which correspond to inclusion criteria 10 and 11. The clinical insomnia inclusion criterion is developed with reference to the Diagnostic and Statistical Manual of Mental Disorders—Fifth Edition (DSM-5 [33]) insomnia disorder diagnostic features. Difficulty initiating sleep is defined by a subjective sleep latency greater than 30 min, difficulty maintaining sleep is defined by frequent awakenings or problems returning to sleep within 30 min after awakenings, and early morning awakening is defined by awakening at least 30 min before the scheduled time and the total sleep time before the awakening is less than 6.5 h. The clinical depression inclusion criterion is based on the modified Chinese version of the Revised Clinical Interview Schedule (CIS-R [34]) algorithm for ICD-10 Mild depressive episode without somatic symptoms (F32.00). The timeframe for items measuring ICD-10 depressive episode has changed from “in the past week” to “in the past 2 weeks” to tap the 2-week requirement for DSM-5 depressive episode diagnostic criteria. In order to meet the criteria of mild depressive episode without somatic symptoms, the participants need to fulfill the following four conditions: (1) having a minimum of 2-week duration of depressive episode; (2) endorsing at least two prominent symptoms of depression—depressed mood, loss of interest, fatigue—in the past 2 weeks; (3) endorsing at least two of the other common depressive symptoms—reduced concentration, reduced self-esteem, ideas of guilt or worthlessness, pessimism about future, suicidal ideation, disturbed sleep, change in appetite with corresponding weight change—in the past 2 weeks; and (4) obtaining a norm-based mental component score of ≤ 45 in the 12-item Short-Form Health Survey Version 1 (SF-12 Version 1) [35]. Because no epidemiological research has been conducted to assess the screening utility of the SF-12 Version 1 mental health component scale for diagnosable depression in Hong Kong Chinese population, the cutoff score of ≤ 45 was chosen with reference to a study that assessed its diagnostic accuracy to predict depression in the general Australian population [36]. In addition, stage 2 telephone diagnostic interview screening is used to reject participants who meet the aforementioned exclusion criteria 2 to 7.

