### Outcomes

#### Primary outcomes

##### Depression severity

The 20-item Center for Epidemiologic Studies Depression Scale [41] is used to measure participants’ severity of depressive symptoms during the past week. Each item is rated on a 4-point Likert scale, ranging from “less than 1 day” to “5–7 days.” It has been validated in a Hong Kong sample and has high internal consistency (Cronbach’s alpha = .85 [42]).

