##### Clinical comorbidity

The number of participants with a current diagnosis of four major comorbidities (generalized anxiety disorder, phobias, obsessive-compulsive disorder, and panic disorder) are estimated from the modified Chinese version of the CIS-R [34] administered in the stage 2 telephone diagnostic interview screening. The modified Chinese version of the CIS-R [34] measures the ICD-10 diagnoses related to generalized anxiety disorder (F41.1), phobias (F40.00, F40.01, F40.1, F40.2), obsessive-compulsive disorder (F42), and panic disorder (F41.0).

Primary outcome assessments take place at baseline, post-intervention, and 6-week follow-up for both CBT-I and waitlist control conditions. The schedule of enrolment, interventions, and assessments is summarized in Table 2.

**Table 2 Tab2:** The Schedule of Enrolment, Interventions, and Assessments

	Screening	Baseline		Allocation	Post intervention		6-week follow-up	
Timepoint (week)	− 12	0		1	7		13	

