**Assessments:**								
*Primary outcome measures*		CBT-I	WLC		CBT-I	WLC	CBT-I	WLC
Depression severity (CES-D)		X	X		X	X	X	X
Insomnia severity (ISI)		X	X		X	X	X	X
Sleep quality (PSQI)		X	X		X	X	X	X
*Secondary outcome measures*		CBT-I	WLC		CBT-I	WLC	CBT-I	WLC
Subjective health (SF-12 Version 1)		X	X		X	X	X	X
Anxiety (HADS-A)		X	X		X	X	X	X
Treatment expectancy (modified CEQ)		X	X		X			X
Treatment acceptability (modified PARS)		X	X		X			X
Demographics	X							
Clinical comorbidity	X							
*Post-screening eligibility assessments*		CBT-I	WLC		CBT-I	WLC	CBT-I	WLC
Withdrawal criteria					X	X	X	X
Cross-condition contamination check						X		X

*CES-D* Center for Epidemiologic Studies Depression Scale, *ISI* Insomnia Severity Index, *PSQI* Pittsburgh Sleep Quality Index, *HADS-A* Hospital Anxiety and Depression Scale—Anxiety subscale, *CEQ* Credibility/Expectancy Questionnaire, *PARS* Participant Acceptability/Usability Rating Scale

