### Sample size

The most updated meta-analysis of 28 self-help CBT-I RCTs [19] showed a significant treatment effect in alleviating depressive symptoms (Hedges’ *g* = 0.35) and insomnia symptoms (Hedges’ *g* = 0.79). It also found that the mean cumulative study attrition rates were 21.25% (SD = 15.31%) and 18.4% (SD = 18.21%) in the treatment and the waiting list/routine care/no treatment/psychoeducation groups, respectively. Hence, a conservative small effect size (Cohen’s *f* = 0.2) and an attrition rate of 30% are estimated for the present study.

The sample size calculation for each of the three primary outcomes (i.e., insomnia severity, poor sleep quality, and depression severity) is based on mixed ANCOVA using GPower 3.1. To conduct a 2 (condition: CBT-I versus waitlist control) × 2 (assessment: baseline versus post-intervention) mixed ANCOVA with an alpha value set at 0.05, two-sided, 80% power to detect a small effect of 0.2 (Cohen’s *f*) between two groups while controlling for 12 covariates (demographics, clinical comorbidity, treatment expectancy, and acceptability of treatment), a total sample size of 199 will be required. In order to account for 30% attrition, a total sample of 285 participants will be sufficient to detect a small effect size (Cohen’s *f* = 0.2) for the difference in the change in each of the three primary outcomes (i.e., insomnia severity, poor sleep quality, and depression severity) from baseline to post-intervention between CBT-I condition and waitlist control condition with a two-sided 5% significance level and a power of 80%.

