### Allocation

One week following the completion of the baseline assessment, participants are randomly assigned in a ratio of 1:1 either to the CBT-I group or the waitlist control group using an online randomized algorithm (https://www.php.net/manual/en/function.random-int.php). The group assignment follows the simple randomization procedure and is completely automated to ensure allocation concealment.

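### A second pre-randomisation ISI score is available from screening, but the adjustment rule would use it only if the arms happened to differ on it; prespecifying it could give a small gain in precision

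*Protocol article*

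**What the plan says.** In the Protocol article, Screening measures, stage 1 records that each participant's "severity of insomnia symptoms is measured by the Insomnia Severity Index" and that "severity of depressive symptoms is measured by the PHQ-9". Both scores have entry cut-offs under Inclusion criteria (ISI at least 8, PHQ-9 at least 10), so every correctly enrolled participant has them.

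The ISI is also one of the three primary outcomes, and "Primary outcome assessments take place at baseline, post-intervention, and 6-week follow-up for both CBT-I and waitlist control conditions". Allocation comes later: "One week following the completion of the baseline assessment, participants are randomly assigned in a ratio of 1:1". Two ISI scores therefore precede randomisation. Table 2 labels screening week -12, baseline week 0 and post-intervention week 7.

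The depression outcome uses a different instrument from screening: "The 20-item Center for Epidemiologic Studies Depression Scale [41] is used to measure participants’ severity of depressive symptoms during the past week". The PSQI has no screening score.

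Two places deal with covariates. Sample size sets power "while controlling for 12 covariates (demographics, clinical comorbidity, treatment expectancy, and acceptability of treatment"). The Data analysis plan models change from baseline to post-intervention in a mixed model. It adjusts for clustering, and for demographic, clinical and outcome variables on which the arms differ significantly at baseline. Neither place names the screening ISI or PHQ-9.

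**The concern.** A pre-randomisation score on the same instrument as a primary outcome is likely to be prognostic, is not affected by treatment, and is complete by design because entry depended on it. Two imperfect readings of a fluctuating symptom can predict the later score better than one. The gain comes from prespecified adjustment. Under the stated rule the score enters only when the arms happen to differ significantly, which selects on chance imbalance rather than on prognostic value.

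This is separate from whether baseline ISI itself should always be adjusted for: settling that would still leave the screening score outside the model. What is at stake is efficiency on one of three primary comparisons. Recruitment is complete, so the choice of covariates is one of the few remaining ways to gain precision.

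**Working it through.** **Inputs from the protocol.** Cohen's f = 0.2, two-sided alpha 0.05, 80% power, 12 covariates, 199 evaluable, 285 after 30% attrition (Sample size); ISI internal consistency 0.81 (Screening measures); weeks -12, 0 and 7 (Table 2).

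**Inputs assumed.** All correlations: r_b (baseline with post), r_s (screening with post) and r_sb (screening with baseline). The protocol gives none.

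**Step 1: the plan's own figure.** With a noncentral F test, 1 numerator degree of freedom and noncentrality N × f² = 199 × 0.04 = 7.96, power at N = 199 is 0.801, and 199 is the smallest N that reaches 0.80. Then 199 / 0.70 = 284.3, rounded up to 285. Both stated figures reproduce.

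**Step 2: formula for the gain.**
- Residual variance, baseline only: 1 - r_b².
- Residual variance, both scores: 1 - R², with R² = (r_b² + r_s² - 2 r_b r_s r_sb) / (1 - r_sb²).
- Power at N = 199: divide the noncentrality by the ratio of the two variances and spend one more degree of freedom. This treats f = 0.2 as already net of baseline adjustment, which the protocol does not say.

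**Step 3: no gain.** With r_b = 0.5, r_sb = 0.6 and r_s = 0.5 × 0.6 = 0.30:
R² = (0.25 + 0.09 - 0.18) / 0.64 = 0.25, the same as r_b². The reduction is exactly 0%. This is pure first-order decay without measurement error.

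**Step 4: fading correlation with measurement error.** Take 0.81 as the reliability of a single reading and let the true state correlate φ over each interval, so r_b = r_sb = 0.81φ and r_s = 0.81φ². As a simplification, φ is the same for both intervals.

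| φ | Reduction in residual variance | Power at N = 199 |
|---|---|---|
| 0.6 | 0.5% | 0.80 |
| 0.7 | 1.2% | 0.81 |
| 0.8 | 2.9% | 0.81 |
| 0.9 | 7.1% | 0.83 |

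Check at φ = 0.9: r_b = r_sb = 0.729 and r_s = 0.656, so residual variance goes from 0.469 to 0.435, and 0.435 / 0.469 = 0.93.

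**Step 5: favourable case, all correlations 0.5.**
R² = (0.25 + 0.25 - 0.25) / 0.75 = 0.333, so residual variance goes from 0.75 to 0.667. The ratio is 0.889, a reduction of 11.1%. Noncentrality is 7.96 / 0.889 = 8.95 and power is 0.845. Equivalently, 199 × 0.889 gives about 177 participants for the same precision.

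**Step 6: PHQ-9 as a proxy for CES-D.** With (r_b, r_s, r_sb) = (0.5, 0.4, 0.6), (0.5, 0.4, 0.5) and (0.6, 0.5, 0.6), the reductions are 2.1%, 4.0% and 4.8%, and power is 0.81 to 0.82.

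**The case against.** The strongest objection is that nothing is misstated: the article omits an optional covariate, and a separate analysis plan may name it. This stands in part. However, the article does not leave adjustment open. It fixes a rule, and that rule admits variables only on a significant difference between arms. The article also already brings screening data into the analysis, since demographics come from stage 1 and comorbidity from stage 2.

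The objection on size stands. Table 2 puts screening 12 + 7 = 19 weeks before the post-intervention score, against 7 weeks for baseline. The ISI covers only two weeks, and entry truncates the screening score at 8. Fading correlation is therefore more plausible than equal correlation, and Step 3 shows that the gain can vanish. The comparator is also kinder than the plan, which does not always adjust for baseline.

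A reader might infer several stronger things that the documents do not support:
- **That the screening scores can never be used.** The clinical characteristics in the adjustment rule could admit one if the arms differed significantly on it.
- **That a large gain is being forgone.** Equal correlations of 0.7 would give 17%, but no correlation is reported and the timing argues against equality.
- **That all three primary outcomes are affected alike.** Only the ISI is repeated on the same instrument. The PSQI has no screening score, and the SF-12, used at stage 2, is scored again at baseline.
- **That the imputation wrongly leaves these scores out.** The article names no imputation predictors at all, and such lists are commonly left to the analysis plan.

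**Conclusion.** The point holds as a modest and optional improvement, chiefly for the insomnia outcome. Two ISI scores precede randomisation, and the stated rule would use the earlier one only after a chance imbalance.

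Against a model that always adjusts for baseline ISI, adding screening ISI lowers residual variance by about 0 to 7% if correlation fades over time, and by about 11% if all correlations equal 0.5. In the equal-correlation case, power at N = 199 goes from 0.80 to about 0.85 at alpha 0.05. Under fading it reaches at most about 0.83. These sizes rest entirely on assumed correlations. For depression, the PHQ-9 proxy gives roughly 2 to 5% under the assumptions in Step 6.

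Omitting the score does not bias the treatment comparison, and the sample size is correct on its own inputs.

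**What to change.** Before outcomes are examined by arm, state that the insomnia model adjusts for both screening ISI and baseline ISI, for all participants and without a significance test. The form matters: model post-intervention ISI with both scores as covariates or, if baseline remains a response in the mixed model, let the screening score interact with time. In that second form, a main effect alone would leave the complete-data contrast in change unaltered.

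Optionally, add screening PHQ-9 alongside baseline CES-D in the depression model. No change is proposed for the PSQI model or for the SF-12 mental score. Naming the screening ISI and PHQ-9 as imputation predictors is a sensible addition.

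The cost is one sentence and one degree of freedom per covariate. Screening data must already be linked to the app data for demographics and comorbidity, so little extra data handling is needed.

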### CBT-I intervention

The self-help CBT-I treatment content is based on the Chinese translated version of a well-established CBT-I treatment manual entitled “Insomnia: A Clinician’s Guide to Assessment and Treatment” [37]. CBT-I aims at changing dysfunctional cognitive beliefs and maladaptive behaviors that contribute to the maintenance of insomnia. The self-help CBT-I treatment is delivered in the Chinese language in six consecutive weekly modules via proACT-S. The duration of each module is around 45 to 60 min. The content of each treatment module is displayed in Table 1.

**Table 1 Tab1:** Content of each weekly CBT-I treatment module

Week 1	Content	Treatment overview
		Predisposing, precipitating, and perpetuating factors of insomnia
	Homework	Dysfunctional beliefs and attitudes about sleep assessment
Week 2	Content	Sleep hygiene
	Homework	Sleep hygiene assessment
Week 3	Content	Basic facts about sleep
		Relaxation therapy
	Homework	Diaphragmatic breathing relaxation (daily practice)
		Sleep diary (at least three diaries per week)
Week 4	Content	Sleep restriction
		Stimulus control
	Homework	Sleep diary (at least three diaries per week)
		Sleep restriction (sleep efficiency ≥ 90%; 15 min per week maximum)
Week 5	Content	Cognitive restructuring
		Constructive worry
		Cognitive distortions
	Homework	Thought record
Week 6	Content	Integration and review of all treatment content
		Shift work

proACT-S has been pilot tested in a sample of 32 Hong Kong Chinese participants and, later, revamped to improve user experience. One current recommendation for engaging app users was to reduce the amount of text and, instead, to use videos to deliver treatment content [38]. Therefore, animations were added to the text-based materials to enhance user experience. Following the literature recommendations [39, 40], more interactive components were incorporated into the app. In particular, proACT-S now provides (a) a clear timeline to indicate the start date for each assessment and treatment module, (b) indicators for module and assessment completion, (c) more prompts for users to follow in completing the weekly homework, (d) a modifiable sleep diary that accommodates the sleep pattern of shift-workers, and (e) individualized homework feedback.

Reasons for discontinuation of CBT-I may include, but are not limited to, the following: (1) participants’ decision to discontinue treatment at any time for any reason and (2) principal investigator’s decision to terminate treatment for the participants’ safety reasons at any time.

### Outcomes

#### Primary outcomes

##### Depression severity

The 20-item Center for Epidemiologic Studies Depression Scale [41] is used to measure participants’ severity of depressive symptoms during the past week. Each item is rated on a 4-point Likert scale, ranging from “less than 1 day” to “5–7 days.” It has been validated in a Hong Kong sample and has high internal consistency (Cronbach’s alpha = .85 [42]).

##### Insomnia severity

The 7-item Insomnia Severity Index [29] is used to assess participants’ severity of insomnia symptoms and the associated daytime impairment over the past 2 weeks. Each item is rated on a 4-point Likert scale, ranging from “not at all” to “extremely.” It has been validated in Hong Kong samples [30, 31] and has high internal consistency (Cronbach’s alpha = .81 [31]).

##### Sleep quality

The 19-item Pittsburgh Sleep Quality Index [43] is used to measure participants’ sleep quality and disturbances during the past month. It has seven components, namely, sleep quality, sleep latency, sleep duration, habitual sleep efficiency, sleep disturbance, use of hypnotics, and daytime dysfunction. Each subscale is converted to a scale of 0 to 3. It has been validated in Hong Kong samples [25] and has good reliability (Cronbach’s alphas range from .59 to .63 [44]).

#### Secondary outcomes

##### Subjective health

The SF-12 Version 1 is used to measure participants’ subjective physical and mental health status. The SF-12 Version 1 is scored using the recommended norm-based scoring with a mean of 50 and a standard deviation of 10 in the general US population [35]. It has been validated in Hong Kong samples [25, 45].

##### Anxiety

The 7-item Hospital Anxiety and Depression Scale—Anxiety subscale [46] is used to measure participants’ severity of anxiety symptoms during the past week. Each item is rated on a 4-point Likert scale. It has been validated in Hong Kong samples [25, 47] and has high reliability (Cronbach’s alpha = .8 [47]).

##### Treatment expectancy

The 6-item Credibility/Expectancy Questionnaire [48] has been modified to measure participants’ cognitively and affectively based expectancy towards the treatment. The original phrase “trauma symptoms” has been changed to “depressive symptoms” or “insomnia symptoms.” Four items are rated on a 9-point Likert scale, ranging from “not at all” to “very.” The remaining two items are rated on a 11-point Likert scale, ranging from “0%” to “100%.” It has been validated in cognitive behavioral therapeutic interventions for people with depression [49] or insomnia [50], and it has high internal consistency (Cronbach’s alphas range from .81 to .96).

##### Acceptability of treatment

The 26-item modified Participant Acceptability/Usability Rating Scale [51] is used to measure participants’ evaluation of the treatment via proACT-S on a 3-point Likert scale, ranging from “agree” to “disagree.” It has been validated in a pilot CBT-I study in Hong Kong [52].

##### Demographics

Information about participants’ age, education level, marital status, occupation, and gender is obtained from the stage 1 online rapid screening.

##### Clinical comorbidity

The number of participants with a current diagnosis of four major comorbidities (generalized anxiety disorder, phobias, obsessive-compulsive disorder, and panic disorder) are estimated from the modified Chinese version of the CIS-R [34] administered in the stage 2 telephone diagnostic interview screening. The modified Chinese version of the CIS-R [34] measures the ICD-10 diagnoses related to generalized anxiety disorder (F41.1), phobias (F40.00, F40.01, F40.1, F40.2), obsessive-compulsive disorder (F42), and panic disorder (F41.0).

Primary outcome assessments take place at baseline, post-intervention, and 6-week follow-up for both CBT-I and waitlist control conditions. The schedule of enrolment, interventions, and assessments is summarized in Table 2.

**Table 2 Tab2:** The Schedule of Enrolment, Interventions, and Assessments

	Screening	Baseline		Allocation	Post intervention		6-week follow-up	
Timepoint (week)	− 12	0		1	7		13	
**Enrolment:**								
Eligibility screening	X							
Informed consent	X	X						
Allocation				X				
